### Tissue collection

2.4.

Written informed consent is obtained from all participants for the collection and analysis of tumor tissue, with both formalin-fixed paraffin-embedded (FFPE) and fresh-frozen specimens collected at surgery. Immunohistochemistry and immunofluorescence analyses are performed on FFPE and fresh-frozen tissue to characterize USPIO uptake across immune and nonimmune cell populations. For extra-axial tumors such as VS, tumors are often completely resected allowing comparison of ferumoxytol imaging datasets with tissue across the entire tumor volume. For intra-axial tumors such as glioma, image-guided tissue sampling of non-enhancing and enhancing regions on delayed phase (>24 hours) post ferumoxytol imaging can be performed using neuronavigation software.

The interval between the final ferumoxytol MRI scan and tissue acquisition will be recorded. Surgery will be scheduled as close as clinically feasible to the final imaging timepoint, determined by clinical urgency, theater availability and standard care pathways. In line with the usual clinical pathway at our institution, for participants with glioma, it is expected, that surgery will be performed within 24 hours of the final MRI scan. For participants with VS, it is expected that surgery will be performed within 4 weeks of the final MRI scan. Acquired imaging from each timepoint (post GBCA and post ferumoxytol) will be fused using neuronavigation software. For participants with glioma, sampling will target regions within the tumor, where safe and appropriate to do so, corresponding to delayed ferumoxytol related changes, contrast enhancement and non-enhancing tumor. For participants with VS, complete or near-complete resection is standard practice at our institution but we will also use neuronavigation to allow for tissue sampling of different regions within the tumor. Sample location will be recorded for later comparison with MRI-derived maps. Imaging–histology registration will be interpreted with recognition of unavoidable spatial uncertainty arising from brain shift, tissue deformation, sampling limitations, fixation and sectioning effects, and differences between *in vivo* MRI resolution and *ex vivo* histological resolution.

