#### Imaging CNS TAMs using USPIO-enhanced MRI

1.1.2.

Considering the role of TAMs in tumor growth, paired with the advent of TAM–targeted cancer immunotherapies, a diagnostic tool capable of detecting, quantifying and monitoring TAM abundance *in vivo* is required. One potential tool, is through ultrasmall superparamagnetic iron oxide (USPIO) nanoparticles (<50 nm), consisting of an iron oxide core surrounded by a carbohydrate or polymer coating [17]. Ferumoxytol is a commercially available USPIO preparation that has FDA approval as an iron replacement therapy and most recently as an MRI contrast agent (Feraheme®, Azurity Pharmaceuticals) [18,19]. The iron USPIO core of ferumoxytol induces strong T_1_ and T_2_/T_2_* relaxation effects, and its size and coat results in a long circulating half-life following intravenous administration (ferumoxytol, t½ = 14–21 hours) [17,20]. Early phase USPIO imaging (<24 hours post-injection) allows for high-resolution MRI angiography whilst circulating in the vasculature. In areas of endothelial disruption, such as within CNS tumors, USPIO slowly (~24–48 hours) extravasates into the tissue extravascular-extracellular space (EES), showing delayed signal enhancement on T_1_-weighted imaging [21]. Ferumoxytol is rapidly phagocytosed by TAMs, as outlined in Figure 1 [22–24]. The engulfment and focal concentration of USPIO within TAMs creates local magnetic susceptibility effects, reducing signal intensity on T_2_* and susceptibility-weighted MRI acquisitions.

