**Figure 1. f0001:**
[figure not shown]
Distribution and biometabolism of USPIO following intravenous administration. Following intravenous injection, USPIO nanoparticles initially circulate within the bloodstream (<24 hours; intravascular phase), producing T_1_and T_2_* shortening. In regions of blood–brain barrier disruption, USPIO extravasate over 24–48 hours into the extravascular space and are phagocytosed by TAMs, leading to intracellular iron accumulation and delayed T_1_and T_2_/T_2_* contrast changes. At later time points (>14 days), USPIO are taken up by the mononuclear phagocyte system, with iron incorporated into systemic iron stores and nanoparticle coatings cleared from the body.

Early studies utilizing USPIO in WHO grade IV gliomas demonstrated additional areas of enhancement on delayed imaging, when compared to standard post-GBCA (gadolinium-based contrast agent) sequences [22]. More recently, post-treatment studies in HGGs undergoing chemoradiotherapy have demonstrated that delayed USPIO-enhanced MRI can differentiate pseudoprogression (transiently increased volumes of contrast enhancement within the radiation field) from true disease progression in IDH-1 (isocitrate dehydrogenase 1) wild-type and IDH-1 mutated tumors [25]. Whilst a growing number of studies have investigated USPIO-related enhancement and uptake in HGGs, no studies have investigated the utility of these clinically available USPIO compounds in diffuse or transforming LGGs [7,25–28]. Therefore, it is unclear how the lesser degree of BBB disruption, and the immune phenotype in these tumors (compared to HGGs), will impact both extravasation of USPIO and its cellular internalization. Whilst early studies have reported isolated cases of USPIO uptake in histologically benign, extra-axial tumors such as meningioma there also remains a paucity of studies in non-astrocytic, extra-axial tumors such as VS that sit outside the blood–brain barrier [29].

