Scan 2 is performed within two hours of the ferumoxytol infusion, and incorporates the same T_1_W imaging, T_1_ relaxivity (R_1_) mapping, SWI, T_2_ and T_2_* mapping and QSM protocol used for the baseline scan. This short (<20 minutes) imaging protocol allows for the evaluation of ferumoxytol-related alterations in brain and tumor vasculature at this early timepoint. Visits 2 and 3 (scans 3 and 4) occur 24 and 48 hours, capturing the expected peak of USPIO uptake in TAMs post-infusion. During these subsequent visits, patients undergo the same brief MRI protocol as conducted at scan 2. This will enable the assessment of delayed (>24 hours) ferumoxytol-related imaging changes relative to baseline.

Since participants receive both GBCA and ferumoxytol, potential interactions between contrast-agent effects will be considered during image interpretation. Prior protocol optimization phantom experiments performed by our group, which demonstrated how GBCA is expected to predominantly influence T_1_-weighted and R_1_ measurements, whereas ferumoxytol is expected to exert stronger effects on T_2_, T_2_*/R_2_/R_2_*, SWI and QSM-derived susceptibility measures (unpublished). Accordingly, GBCA-enhanced imaging will primarily be used to define conventional enhancement and permeability-related tumor regions, while delayed ferumoxytol assessment will prioritize T_2_, T_2_*/R_2_/R_2_*/SWI and QSM-derived measures. The acquisition of R_1_, R_2_, R_2_*, T_2_*, T_2_, SWI and QSM data across pre-contrast, post-GBCA, early post-ferumoxytol and delayed post-ferumoxytol timepoints will also allow the *in vivo* signal effects of each contrast agent to be assessed across complementary quantitative imaging markers.

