### Tissue analysis

2.6.

Resected specimens will be analyzed using established immunohistochemical protocols [14,38]. FFPE sections will be stained to quantify TAM density (Iba1), vascular features (CD31, fibrinogen), and Schwann cell markers (CD56). Ferumoxytol deposition within resected tissue will be assessed using Perls’ Prussian blue staining for iron and immunolabelling of the dextran ferumoxytol coating (Dx1). The cellular localization of ferumoxytol uptake will be further characterized using dual immunohistochemistry and immunofluorescence. Laser ablation inductively coupled plasma mass spectrometry (LA-ICP-MS) will also be used to detect and spatially map iron derived from USPIO uptake within resected tumor tissue [39–41]. To evaluate in detail the phenotype and spatial distribution of TAMs in each tumor and their relationship to USPIO uptake, selected tissue specimens will be analyzed using imaging mass cytometry and a previously validated antibody panel [11,42].

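### VS tissue may be taken up to about 30 days after infusion, past the 14-day mark in Figure 1, so the secondary MRI comparisons with Dx1 and tissue iron may be distorted by elapsed time

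*Protocol article*

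**What the plan says.** Section 2.3.1 places the delayed scans as follows: "Visits 2 and 3 (scans 3 and 4) occur 24 and 48 hours, capturing the expected peak of USPIO uptake in TAMs post-infusion". Section 2.4 then sets different expectations for tissue. For glioma, "surgery will be performed within 24 hours of the final MRI scan"; for the other group, "For participants with VS, it is expected that surgery will be performed within 4 weeks of the final MRI scan". The same section says that the interval from last scan to tissue will be recorded and that surgery will follow the last scan as soon as clinical circumstances allow.

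The Figure 1 caption (section 1.1.2) describes a late phase, more than 14 days after injection, in which phagocytes take up the agent. It gives the outcome as "with iron incorporated into systemic iron stores and nanoparticle coatings cleared from the body".

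Section 2.6 measures TAM density by Iba1. Ferumoxytol in tissue is measured separately, by Perls' stain for iron, by "immunolabelling of the dextran ferumoxytol coating (Dx1"), and by LA-ICP-MS iron maps. Section 2.9 relates imaging to tissue by Pearson or Spearman correlation and mentions neither adjustment for, nor restriction by, the interval.

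**The concern.** The MRI records uptake at 24 and 48 hours. The tissue measures of retained agent record whatever is still there on the day of surgery. In glioma these moments are about a day apart. In VS they may be weeks apart, in a period when the article's own caption says the coating is gone and the iron has moved elsewhere.

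A VS tumor that took up the agent at 48 hours but was resected late could therefore be Dx1-negative, and would then look like a tumor without uptake. This bears on two secondary endpoints in section 1.2: QSM against tissue iron abundance and localization, and TAM phenotype against USPIO uptake. It also bears on the use of LA-ICP-MS as spatial validation in section 2.8. A difference between VS and glioma in retained agent could reflect biology or sampling time. Section 2.4 lists limits of the imaging-histology match, but all of them are spatial; loss of agent over time is not among them.

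**Working it through.** The plan states no figure for this point, so there is none to reproduce. The check is day arithmetic, followed by an illustration on stated assumptions.

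**1. Timing (2.3.1, 2.4, Figure 1)**
- Infusion to surgery = 2 days (48 h) + interval after the last scan.
- Glioma: 2 + 1 = 3 days at most, if the expectation is met.
- VS: 2 + 28 = 30 days at most, if the expectation is met.
- Day 14 after infusion is 14 − 2 = 12 days after the last scan.
- VS window beyond day 14: 30 − 14 = 16 of 28 days (57%). Glioma: none.
- The two windows, days 2–3 and days 2–30, share 1 day. A model adjusting for time could hardly separate tumor type from time since infusion.

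**2. Which measures depend on retained agent**

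| Measure | Depends on retained agent? | Caption beyond 14 days |
|---|---|---|
| Iba1 (TAM density) | No | Not applicable |
| Dx1 | Yes, coating | Coating cleared |
| Perls', LA-ICP-MS | Yes, iron | Iron moved into systemic stores, not said to be cleared |

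For Dx1 the likely direction is toward no uptake. For iron the document does not settle it: the methods could miss iron that has moved away or count iron no longer tied to the agent.

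**3. What the half-life can and cannot say**

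Section 1.1.2 gives "ferumoxytol, t½ = 14–21 hours", a circulating value. Fraction left in plasma = 0.5^(t/half-life). At 48 h: 0.5^(48/14) = 9% to 0.5^(48/21) = 21%. At 14 days (336 h) it is at most 0.5^(336/21) = 0.5^16, about 0.002%. So a late specimen shows only what the tissue kept, and the article gives no rate for that.

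**4. Illustration (assumed, not from the document)**

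Assume exponential tissue loss, a true correlation of 0.70 on the log scale, a log-scale SD of 0.5 for the tissue measure, and VS surgery spread evenly over days 2–30. Then the variance of the interval is 28²/12 = 65.3 and

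r = 0.70 × 0.5 / √(0.25 + (ln 2 / half-life)² × 65.3).

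A simulation gave the same values to two decimals:

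| Assumed tissue half-life | Mean retained, days 2–30 | Retained at day 3 | r, days 2–30 |
|---|---|---|---|
| 3 days | 10% | 50% | 0.18 |
| 7 days | 28% | 74% | 0.37 |
| 14 days | 49% | 86% | 0.55 |
| 28 days | 69% | 93% | 0.65 |
| No loss | 100% | 100% | 0.70 |

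If every VS patient had the same interval, even 30 days, r would stay at 0.70 and only the level would fall. Within VS, attenuation comes from variation in the interval, or from signal falling below detection, not from delay as such.

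**The case against.** The strongest reply has four parts.

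- **The caption is a schematic of whole-body fate.** It gives no retention time for agent already inside tumor macrophages. This stands. It limits the claim to a possible distortion; with no tissue loss the correlation does not change.
- **Four weeks is an upper expectation.** Surgery is to follow the last scan as soon as it can, so many VS specimens may come before day 14. This stands. A reader might take 57% as the share of late specimens, but that would need an even spread of surgery dates, which the document does not state.
- **Tumor-type comparisons are already exploratory** (2.7, 2.9), and iron is assessed by more than one method. This lowers the stakes. It does not help a reader tell late sampling from no uptake.
- **The use of a recorded covariate is ordinary analysis-plan material.** Its absence from an article would not be a finding by itself. The point here is that the timing, assays and correlation method the article does state sit badly with its own caption, and that its discussion of imaging-histology limits omits time.

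A reader might also infer that the caption says both coating and iron are cleared, so that all VS tissue comparisons are biased toward no uptake. The caption says that only of the coating.

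**Conclusion.** The point holds in limited form. The VS tissue window runs to about day 30 after infusion, past the article's own 14-day mark, while glioma tissue is taken by about day 3. Secondary VS comparisons of MRI with Dx1 may be shifted toward no uptake. Those with Perls' and LA-ICP-MS iron may be distorted in an unknown direction. VS-versus-glioma differences in retained agent cannot be separated from time since infusion.

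The size cannot be derived from the document. The correlations of 0.18 to 0.65 rest on assumed tissue half-lives of 3 to 28 days and evenly spread surgery, and show only what is possible.

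The document does not support the inference that the primary endpoint is compromised. That endpoint uses TAM density by Iba1, which does not need the agent to be present at surgery. The document also gives no ground for excluding all specimens after day 14 from the main analysis: the cut-off comes from a figure caption on whole-body fate.

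**What to change.** Surgical timing need not change; the changes concern the text and the analysis.

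1. Reconcile the Figure 1 caption with section 2.4. State what the caption is taken to imply for agent held in VS tissue over the expected interval, and add elapsed time to the listed limits of the imaging-histology comparison.
2. In section 2.9, pre-specify that the Dx1, Perls' and LA-ICP-MS comparisons with MRI are done within tumor type. Use the recorded scan-to-surgery interval plus 48 hours as a stratum or an adjustment, for example by partial Spearman correlation. The Iba1 analysis needs no such term on this ground.
3. Add a sensitivity analysis of these comparisons limited to VS specimens taken within 14 days of infusion.
4. State that a negative Dx1 or iron result in a later specimen is not evidence of no uptake. Adjustment cannot recover signal that has fallen below detection, so this statement is needed as well.

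**Cost.** No new data, since the interval is already recorded. Adjustment loses some precision, and the restricted analysis may hold few specimens: at most 24 VS participants are planned, and section 2.2 includes some being considered for bevacizumab or surveillance rather than surgery.

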### Outcomes

2.5.

#### Post-scan processing

2.5.1.

Post-contrast T_1_-weighted images acquired following both gadolinium-based contrast agent administration and delayed ferumoxytol imaging (24–48 hours post-injection) will be used to delineate tumor regions of interest (ROI). Tumor segmentation will be performed using semi-automatic approaches in ITK-SNAP [32,33]. Diffusion tensor imaging (DTI) data will be processed to derive fractional anisotropy (FA) and mean diffusivity (MD) maps following eddy-current and motion correction. Multi-delay arterial spin labeling (ASL) will be used to generate quantitative cerebral blood flow (CBF) maps. Amide proton transfer (APT) imaging will be processed to obtain magnetization transfer ratio asymmetry maps. Susceptibility-weighted imaging (SWI), DCE-MRI, and additional quantitative MRI modalities will be processed using established pipelines as described below.

Dual-injection dual-temporal-resolution DCE-MRI data will be analyzed using the LEGATOS method [34] to derive high-spatial-resolution maps of the following key microvascular parameters: volume transfer constant (*K*^*trans*^), plasma volume fraction (_*Vp*_) and extravascular extracellular volume fraction (_*Ve*_). SWI data acquired at each timepoint will be analyzed using the ‘Segregation and Extravascular Localization of Ferumoxytol Imaging’ (SELFI) formula, which aims to characterize USPIO nanoparticle intra/extravascular compartmentalization [27]. SWI magnitude images acquired at pre-contrast, early post-ferumoxytol, and delayed post-ferumoxytol time points will be co-registered to non-contrast-enhanced T_1_-weighted images. Voxel-wise logarithmic signal intensity ratios will be calculated between pre-contrast and ‘early’ SWI maps or delayed post-contrast images to estimate relative USPIO concentrations. Subtraction of delayed from early ratio maps will yield positive SELFI^+^ and negative SELFI^–^ values. SELFI^+^ values are thought to reflect extravascular USPIO uptake localized to phagocytic cells (TAMs), whereas SELFI^–^ values indicate persistent intravascular USPIO signal, consistent with regions of higher microvascular density [27]. SELFI values will be compared with maps of quantitative relaxometry values (T_2_*, T_2_) generated using existing pipelines and QSM-derived susceptibility maps. As the SELFI method is an investigational approach and not yet an established clinical biomarker, it may be influenced by image registration error, susceptibility artifact, baseline hemorrhage or calcification, residual intravascular USPIO, and nonlinear signal behavior on SWI magnitude images. SELFI maps will therefore be interpreted alongside QSM, T_2_*, SWI and tissue-based measures rather than as a stand-alone marker of cellular USPIO uptake.

During the study, a QSM protocol for visualizing absolute local magnetic field susceptibility changes resulting from cellular USPIO compartmentalization, will be optimized and evaluated. QSM differs from traditional hypo-intensity contrast in SWI or T_2_*, reflecting local rather than regional tissue susceptibility, overcoming blooming artifacts that arise through incorporating a dipole deconvolution during processing [35,36]. QSM data will be analyzed using the Morphology Enabled Dipole Inversion (MEDI) toolbox (v.2020), a widely validated pipeline for processing complex gradient echo data [36,37]. Early timepoint QSM maps are expected to reflect susceptibility shifts predominantly related to intravascular USPIO, whereas delayed maps (24 and 48 hours post-injection) are hypothesized to capture both residual intravascular USPIO and susceptibility effects, attributable to extravascular uptake by TAMs. Susceptibility values and spatial distribution patterns will be quantified across timepoints and evaluated alongside other multimodal maps, including DCE-MRI parameters and tissue data, to further explore the relationship between susceptibility changes, TAM infiltration and microenvironment features such as permeability and perfusion.

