#### The role of TAMs in the growth and progression of CNS tumors

1.1.1.

Low-grade gliomas (LGGs), including diffuse astrocytomas, account for approximately 10–20% of all primary brain tumors. Although they are more indolent relative to grade III (anaplastic) or grade IV tumors including glioblastomas (GBMs), over 95% of LGGs will undergo malignant transformation into a higher grade (III/IV) gliomas (HGGs) [2]. Depending on tumor location, glioma typically present with seizures, focal neurological signs, or symptoms of raised intracranial pressure and these tumors have a disproportionate impact on patients and wider society, often affecting young adults [3]. In other non-CNS cancers, TAMs are known to be pivotal in driving malignant transformation and may contribute to an LGG’s propensity for infiltration, recurrence and therapy resistance [4–7]. Currently, the appearance of focal contrast enhancement within these tumors, suggestive of loco-regional blood–brain barrier (BBB) disruption, is the most used sign of tumor progression in clinical practice. However, this lacks specificity, with the temporal relationship between histological transformation and appearance of new contrast enhancement unclear [8,9].

VS are histologically benign tumors, arising from Schwann cells lining the vestibulocochlear nerve at the cerebellopontine angle [10]. Whilst 95% occur as a unilateral, sporadic tumor, they can also occur bilaterally as part of the syndrome NF2-related Schwannomatosis (NF2-SWN) [11]. The associated morbidity of VS and their treatment (surgery or radiosurgery) makes management through surgery or radiotherapy particularly challenging [12]. *Ex vivo* VS tissue analysis studies have shown that TAMs compartmentalize within Antoni type B areas and are associated with increased tumor size and growth rate [13]. *In vivo* evidence for increased TAM-dependent inflammation with growing VS also stems from TSPO positron emission tomography (PET) studies, where inflammation in growing tumors is attributed to the abundance of TAMs [13]. Subsequent work demonstrated that TAMs are a targetable driver of the immune microenvironment and tumor growth in NF2-SWN-associated VS also [14–16].

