Our specific hypotheses include that: (1) early (<2 hours) USPIO-enhanced imaging will principally reflect vascular distribution and will correspond with other MRI-derived measures of tumor vascular density and perfusion; (2) delayed (24–48 hours) USPIO-enhanced imaging will principally reflect intracellular USPIO distribution within TAM, and will co-localize with but also extend beyond imaging (GBCA enhancement) and tissue markers of endothelial disruption; (3) that QSM-derived susceptibility estimates and T2*-based measures will provide optimal quantitative reliable measures of TAM density, iron abundance and cellular iron localization with imaged tumors; (4) susceptibility based measures of delayed USPIO uptake (e.g., QSM, R2* mapping) will be greater in growing VS, relative to non-growing tumors, and will reflect an increased abundance of TAM in these tumors; and (5) that regions of higher grade transformation within imaged glioma will show changes on delayed USPIO-enhanced acquisitions, in particular susceptibility-based measures such as QSM, and these regions will show greater TAM abundance on matched tissue sections compared to non-enhancing tumor regions.

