### Eligibility criteria

2.2.

Two main tumor groups of participants will be recruited for this study.

Group A: Patients with either sporadic or NF2-SWN-associated VS. The sample will include growing tumors that are being considered for surgical resection (sporadic tumors) or treatment with the anti-angiogenic agent bevacizumab (NF2-SWN-associated VS), and non-growing/static tumors that are being considered for either further radiological surveillance or surgery.

Group B: Patients with a suspected transforming LGG. Patients in this cohort will have a suspected diagnosis of an LGG on conventional clinical imaging, with or without radiological features suggestive of malignant transformation toward either grade III (anaplastic) or grade IV gliomas. Patients who are listed to undergo surgical debulking or biopsy will be enrolled into the study so that acquired imaging can be compared with tissue datasets.

*Inclusion criteria*:
Be at least 16 years oldHave a CNS tumor suspected to be one of the defined histological typesBe able to lie still for up to 1 hour comfortably

*Exclusion criteria*:
Life expectancy of <1 yearPrevious CNS radiotherapy/stereotactic radiosurgery (SRS)Pregnancy/ breastfeeding in femalesAn eGFR of <30 ml/minA documented history of iron overload/hemosiderosis/hemochromatosisPresence of other immune or inflammatory conditions e.g., rheumatoid arthritisAbsolute (e.g., pacemaker) or relative (severe anxiety or claustrophobia) contraindications to MRI scanningA history of allergic reaction to iron or dextranA history of allergic reaction to gadolinium contrast agents, asthma or renal problemsInability to understand verbal explanations or written information given in English.

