**Figure 2. f0002:**
[figure not shown]
Study design and scanning workflow.

On the first visit, patients undergo a baseline advanced MRI protocol at 3T, including: structural T_1_W and T_2_ FLAIR imaging (glioma only), baseline T_1_ relaxivity (R_1_) mapping (measured using a variable flip angle acquisition), SWI, T_2_ and T_2_* mapping, QSM, and DTI. Amide proton transfer (APT) imaging, a chemical exchange saturation transfer MRI technique that is sensitive to changes in proteins and peptides containing amide groups in tissue, is also performed for recruited glioma patients. It is not performed for participants with VS, as its application in the inferior brain and skull base is often limited by artifacts arising from B_0_ field inhomogeneities at air–tissue interfaces, particularly near the paranasal sinuses and external auditory canals [31]. For measuring tumor perfusion and tumor microvascular characteristics (including endothelial permeability) a multi-delay ASL acquisition and a dual-injection, dual–temporal resolution DCE-MRI acquisition is also collected. During the DCE-MRI protocol, administration of a GBCA (gadoterate meglumine; Dotarem®, Guerbet S.A.; dose of 0.2 mmol/kg) is performed, and is followed by post-contrast T1W imaging and repetition of the pre-contrast T_1_, T_2_ and T_2_* mapping, SWI, and QSM protocols. An overview of included sequences and acquisition parameters are provided in Supplementary Table S1.

After the initial baseline MRI scan, patients receive ferumoxytol at a dose of 5 mg/kg (up to maximum dose of 510 mg) as a slow intravenous infusion over 30 minutes. Patient observations (blood pressure, heart rate, temperature) are performed regularly during the infusion and up to 30 minutes afterward, due to a small risk of serious hypersensitivity reactions following IV iron infusions.

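### In glioma, a whole-tumor ROI drawn on post-contrast T1 images will tend to follow enhancement and, on the delayed scan, is partly selected on ferumoxytol signal

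*Protocol article*

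**What the plan says.** All references are to the protocol article.

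- **Source of the ROI (2.5.1 Post-scan processing).** T1-weighted "images acquired following both gadolinium-based contrast agent administration and delayed ferumoxytol imaging", the latter at 24 to 48 hours, "will be used to delineate tumor regions of interest (ROI"). Segmentation is semi-automatic in ITK-SNAP. No other image is named as a source.
- **Use of the ROI (2.9 Statistical analysis).** There are two uses. Dice, Jaccard and SSIM compare the post-gadolinium ROI with the delayed-ferumoxytol ROI. Separately, T2, T2*, R1 and QSM susceptibility are followed over time, by voxel and in the whole-tumor ROI.
- **Available non-contrast image (2.3.1 Imaging protocol).** Baseline imaging includes T2 "FLAIR imaging (glioma only"). No section gives FLAIR a role in segmentation.
- **Glioma population (2.2 Eligibility criteria).** Suspected low-grade gliomas enter "with or without radiological features suggestive of malignant transformation toward either grade III (anaplastic) or grade IV gliomas". Section 1.1.1 names "the appearance of focal contrast enhancement within these tumors" as the sign of progression most used in practice.
- **Non-enhancing tumor.** In hypothesis 5 (1.2 Objectives), "these regions will show greater TAM abundance on matched tissue sections compared to non-enhancing tumor regions". For tissue, section 2.4 targets regions "corresponding to delayed ferumoxytol related changes, contrast enhancement and non-enhancing tumor", where safe, and records sample locations.

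**The concern.** Two things follow if section 2.5.1 is applied as written.

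First, a glioma without signs of transformation, or the non-enhancing part of one that has them, may show little on either post-contrast T1 image. An outline based on those images will tend to be an outline of enhancement. Section 2.9 nevertheless treats it as the whole tumor.

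Second, a mask drawn on the delayed ferumoxytol image includes voxels partly because ferumoxytol raised their signal. Measuring the effect of ferumoxytol inside that mask is then partly selection on the outcome.

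At stake are the whole-tumor temporal and subgroup estimates in glioma. Section 2.7 intends this pilot to supply preliminary effect sizes for larger studies. Its stated effect sizes concern imaging–histology associations, but the USPIO-sensitive metrics themselves are also to be evaluated there, and estimates taken from enhancement-selected regions would not describe whole tumors.

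**Working it through.** The plan states no figure on this point, so there is none to reproduce. The check sets the sections side by side and then illustrates size on assumed inputs.

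**Step 1: does the outline depend on enhancement?** Section 2.5.1 names only post-contrast T1 images. The overlap analysis in 2.9 compares the volumes of the two masks, which is informative only if each mask follows what its agent enhances. Section 1.1.2 says that delayed T1 enhancement arises where the endothelium is disrupted, and that the effect of the milder barrier disruption in low-grade glioma on extravasation is unclear. The delayed image therefore cannot be relied on to show the tumor that gadolinium misses.

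**Step 2: which mask feeds the temporal metrics?** Section 2.9 does not say. With the gadolinium mask, the enhancement problem remains but the mask is not selected on ferumoxytol signal. With the ferumoxytol mask, both problems apply.

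**Step 3: whole tumor versus enhancing region (assumed inputs).** Let f be the enhancing fraction of the lesion and k the mean change in non-enhancing tumor divided by that in enhancing tumor. Then

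enhancing-region mean / whole-tumor mean = 1 / (f + (1 − f)k).

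Example: a 20 mL lesion with 4 mL changing by 0.10 ppm and 16 mL by 0.01 ppm. The whole-tumor mean is (4 × 0.10 + 16 × 0.01)/20 = 0.028 ppm, and 0.10/0.028 = 3.6. Other inputs give less:

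- f = 0.5, k = 0.1: 1/0.55 = 1.8
- f = 0.5, k = 0.5: 1/0.75 = 1.3
- f = 0.8, k = 0.5: 1/0.90 = 1.1
- k = 1: 1.0, no difference

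**Step 4: selection on the delayed T1 signal (assumed inputs).** Suppose the mask keeps the fraction q of tumor voxels with the highest delayed T1 signal, and a metric has voxel correlation ρ with that signal. Under bivariate normality the mean inside the mask, relative to the whole tumor, shifts by

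ρ × φ(c)/q SD, with c = z(1 − q).

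The factor φ(c)/q is 0.318/0.25 = 1.27 at q = 25%, 0.399/0.50 = 0.80 at q = 50%, and 0.318/0.75 = 0.42 at q = 75%.

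| ρ | q = 25% | q = 50% | q = 75% |
|---|---|---|---|
| 0 | 0 | 0 | 0 |
| 0.2 | 0.25 | 0.16 | 0.08 |
| 0.4 | 0.51 | 0.32 | 0.17 |
| 0.6 | 0.76 | 0.48 | 0.25 |
| 0.8 | 1.02 | 0.64 | 0.34 |

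R1 reflects the same T1 effect on which the mask is drawn, so the selection is direct. T2, T2* and QSM are different contrasts from the same agent at the same time, so for them it is indirect. The documents give neither ρ nor q.

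**The case against.** The strongest reply is that this is a detail a condensed article leaves to the full protocol. Section 2.5.1 does not say that only these images are used or that the ROI equals the enhancing voxels, and it sets no threshold. Section 2.9 speaks of the whole tumor, which suggests that a full outline is intended. This is fair as far as intent goes. But the article does not stay silent on the source: it names one, and that source does not suit the use made of it in glioma.

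Several further objections stand and limit the point.

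- A reader might infer that hypothesis 5 has no comparator. The documents do not support that: section 2.4 samples non-enhancing tumor and records the location, and the hypothesis compares TAM abundance in matched tissue.
- A reader might infer that hypothesis 2 cannot be tested. Its imaging comparison of gadolinium and delayed ferumoxytol extent needs one mask per agent, so the two T1 masks are right for that purpose.
- A reader might conclude that patients without enhancement drop out. No section says so.
- Circularity is direct only for R1 and delayed T1 volume. Section 2.3.1 gives priority to T2, T2*, SWI and QSM for delayed assessment.
- The primary imaging–tissue association is less exposed, at least in glioma, because image values can be read at recorded sample locations.

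**Conclusion.** The concern holds for the ROI-based temporal, subgroup and whole-tumor analyses in the 15 planned gliomas. There the outline will tend to represent enhancing tumor and, if taken from the delayed ferumoxytol image, is partly selected on the agent being measured. The 24 planned VS participants are less affected.

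The size cannot be stated from the documents. The selection shift runs from none at zero correlation to 1.02 SD at ρ = 0.8 and q = 25%; at ρ = 0.4 it is 0.17 to 0.51 SD. These figures assume normality and a mask cut on T1 signal, which a semi-automatic outline only approximates. The ratio in step 3 contrasts two different quantities. It is an error only when the enhancing-region value is reported as the whole-tumor value, and its 3.6 comes from one assumed lesion.

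Neither the tissue comparison in hypothesis 5 nor the gadolinium-versus-ferumoxytol overlap analysis is invalidated.

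**What to change.** Amend section 2.5.1, with a matching line in 2.9, before the delayed images are analysed, so that the choice of mask is not driven by the data:

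1. For glioma, outline one whole-tumor ROI per patient on baseline T2 FLAIR with pre-contrast T1. For VS, outline it on the scan-1 post-gadolinium T1 image.
2. Propagate that mask by registration to all four scans and use it for the temporal, subgroup and whole-tumor metrics.
3. Keep the gadolinium-T1 and ferumoxytol-T1 masks as sub-regions for the overlap analysis.
4. Define non-enhancing glioma as the FLAIR ROI minus the gadolinium-enhancing mask.

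The images are already part of the protocol. The cost is extra segmentation of 15 gliomas and the registration work. The drawbacks are some registration error and FLAIR outlines that may include edema.
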